## Abstract

**Background:**

SAIATU is a program of specially trained in-home social assistance and companionship which, since February 2011, has provided support to end-of-life patients, enabling the delivery of better clinical care by healthcare professionals in Osakidetza (Basque Health Service), in Guipúzcoa (Autonomous Community of the Basque Country).

In January 2012, a retrospective observational study was carried out, with the aim of describing the characteristics of the service and determining if the new social service and the associated socio-health co-ordination had produced any effect on the use of healthcare resources by end-of-life patients.

The results of a comparison of a cohort of cases and controls demonstrated evidence that the program could reduce the use of hospital resources and promote the continuation of living at home, increasing the home-based activity of primary care professionals.

The objective of this study is to analyse whether a program of social intervention in palliative care (SAIATU) results in a reduction in the consumption of healthcare resources and cost by end-of-life patients and promotes a shift towards a more community-based model of care.

**Method/design:**

Comparative prospective cohort study, with randomised selection of patients, which will systematically measure patient characteristics and their consumption of resources in the last 30 days of life, with and without the intervention of a social support team trained to provide in-home end-of-life care.

For a sample of approximately 150 patients, data regarding the consumption of public healthcare resources, SAIATU activity, home hospitalisation teams, and palliative care will be recorded. Such data will also include information dealing with the socio-demographic and clinical characteristics of the patients and attending carers, as well as particular characteristics of patient outcomes (Karnofsky Index), and of the outcomes of palliative care received (Palliative Outcome Scale).

Ethical approval for the study was given by the Clinical Research Ethics Committee of Euskadi (CREC-C) on 10 Dec 2012.

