## Methods/design

### Hypothesis

The intervention of SAIATU (a resource for the social support of end-of-life patients) improves efficiency in the use of healthcare resources in end-of-life patients, decreasing the consumption of hospital resources and increasing the home-based activities conducted by Primary Care in the last 30 days of life.

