### Location and date of study

The study will be conducted in the provinces of Guipúzcoa.

Period of study: September 2012 - October 2013.

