#### Phase 2. Study of PROSPECTIVE cohorts, assigned by randomised blocks

The study will be initiated with two cohorts:

1.
***Exposed cohort*****:** comprising patients who will be attended by SAIATU, without prejudice to the care received from the public health system.

2.
***Control cohort*****:** comprising patients who will be cared for exclusively through the public health system.

The evolution of the disease over the course of the study will determine the different healthcare mechanisms (Primary Care, Specialised Care (SC), Home Hospitalisation (HH)) that will intervene in the care of each patient, so that, at the end of the study, the two initial cohorts will be divided into 4 subgroups:

1)
*Exposed cohort*

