### Population for Study

This study will comprise oncology patients from the health districts of Guipúzcoa, attended by the Basque Health Service.

Assuming that 2,500 people per million population die each year from malignant neoplasm, and taking into account that the population of Guipúzcoa is 709,607 inhabitants, it is estimated that the eligible population for this study is 1,774 deaths from malignant neoplasm per year. For a period of 10 months of prospective study, this corresponds to a population of 1,478 deaths from malignant neoplasm in these provinces.

Although the final number of patients for inclusion will be calculated during the design of the prospective study itself, after the results of Phase 1, it is estimated that the resulting sample size could allow some 150 patients to be studied. This sample, which would correspond to 10% of the total population of deaths from cancer in this period, would strengthen the study’s feasibility with respect to its representativeness of the total population in both provinces.

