### Criteria for inclusion and exclusion from the study sample population

Criteria for inclusion:

- Documented presence of incurable, progressive and advanced oncological disease, capable of systematic treatment in the home.

- Little or no possibility of response to oncological treatment with a curative intent.

- Limited life prognosis.

- Presence of a principal carer.

Criteria for exclusion:

- Death or disability of the family carer.

- Withdrawal from the Basque public health system

- Absence of compliance with informed consent.

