### Analysis of variables

The parameters will be analysed using the statistical software SPSS 15.0 for Windows.

A descriptive study will be conducted on the *consumption of healthcare resources* by subgroup in the last 30 days of life. The descriptive study will include measures of central tendency, confidence intervals at 95% for the population mean, and contingency tables (frequencies) for each of the recorded variables.

Each subgroup will be analysed by age, sex, and main diagnosis.

For the comparison of proportions, Pearson’s Χ^2^ test, or, when appropriate, Fisher’s exact test will be used to calculate relative risk (RR), absolute risk reduction (ARR) and the number needed to treat (NNT) with 95% confidence interval.

The Student T-test will be applied to calculate the equality of means for independent samples in the case of continuous variables, upon confirmation of the conditions of normality and homoscedasticity.

The quantification of costs incurred by the SAIATU program will be calculated on the basis of the activities performed by the program’s professionals, measured in hours of care. Based on the actual time spent on patients, the total cost will be distributed between each of the activities.

Calculations of unit costs per activity, taking into account the number of times each activity is performed for the period under analysis, will finally be performed.

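### The randomised comparison counts resource use back from death: patients alive at close have no outcome, and early deaths bring in days before assignment

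*Protocol article*

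**What the plan says.** The window appears in three places in the protocol article. The abstract (Method/design) describes a study "which will systematically measure patient characteristics and their consumption of resources in the last 30 days of life". The Hypothesis section predicts less hospital use and names "increasing the home-based activities conducted by Primary Care in the last 30 days of life". Analysis of variables describes consumption of healthcare resources "by subgroup in the last 30 days of life".

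The same window is used in Phase 1, a retrospective cohort of people who died from malignant neoplasm. Phase 1 is also to supply the basis for the Phase 2 sample size.

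Phase 2 is headed "Study of PROSPECTIVE cohorts, assigned by randomised blocks", so patients are assigned while alive. The entry criterion on survival is "Limited life prognosis", with no lower or upper bound. Population for Study gives the follow-up: "For a period of 10 months of prospective study". No section starts the window at assignment, limits it to days after assignment, or says what happens to a patient who is alive at the end.

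**The concern.** A window counted back from death is always defined in a cohort of decedents. In a prospective randomised comparison it depends on an event after assignment, and three things follow.

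- A patient alive at close has no last 30 days, and so no value for the main variable.
- A patient who dies *t* days after assignment, with *t* below 30, brings in 30 − *t* days from before assignment. These should be alike in the two cohorts on average, so they shrink any true difference.
- Use between assignment and the last 30 days does not enter the test of the hypothesis. If SAIATU moved a hospital stay from the last month to the month before, the comparison would show a reduction where none occurred.

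The study is meant to confirm or refute the pilot's finding of lower hospital use. A diluted result could hide a real effect, and a shift in timing could be read as a saving.

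**Working it through.** **The plan's own figures.** 2,500 deaths per million × 0.709607 million = 1,774 per year; × 10/12 = 1,478 in 10 months; 150 / 1,478 = 10.1%. All three reproduce. The 150 itself cannot be derived, because the article gives no variance, difference or proportions and leaves the final size until after Phase 1.

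**By logic alone.** A patient who dies 10 days after assignment has 30 − 10 = 20 window days before assignment. A patient who dies on day 120 has days 0 to 90 outside the window. A patient alive at close has no window.

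**Size, under assumptions.** The article gives the 10-month prospective phase and the 30-day window. Everything else here is assumed: median survival from assignment *m* of 1 to 4 months, uniform enrolment over the first *E* = 5, 8 or 10 months, cut-off at month 10, and either a constant hazard (exponential) or a rising one (Weibull, shape 2).

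Share alive at close = (1/*E*) × ∫ S(t) dt from 10 − *E* to 10. Here S(t) = exp(−ln 2 · t/*m*) for constant hazard and exp(−ln 2 · (t/*m*)²) for rising hazard. Example with constant hazard, *m* = 2, *E* = 10: the rate is ln 2 / 2 = 0.3466, and (1 − exp(−3.466)) / 3.466 = 0.969 / 3.466 = 28%.

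Share of counted days before assignment = 1 − mean of min(T, 30)/30 among those who died by close, with T the days from assignment to death. This was simulated with 2,000,000 patients per cell.

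Each cell shows % alive at close / % of counted days before assignment:

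| Hazard, enrolment | m = 1 | m = 2 | m = 3 | m = 4 |
|---|---|---|---|---|
| Constant, 10 months | 14 / 31 | 28 / 21 | 39 / 17 | 47 / 15 |
| Constant, 8 months | 4 / 29 | 17 / 18 | 29 / 15 | 38 / 13 |
| Constant, 5 months | 1 / 28 | 8 / 17 | 19 / 13 | 28 / 11 |
| Rising, 10 months | 11 / 20 | 21 / 6 | 32 / 3 | 42 / 2 |
| Rising, 8 months | 0 / 19 | 6 / 6 | 17 / 3 | 29 / 2 |
| Rising, 5 months | 0 / 19 | 0 / 5 | 3 / 3 | 12 / 2 |

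Within each row the two problems run in opposite directions: short survival adds days before assignment, and long survival adds patients without an outcome. Some cells, such as rising hazard with enrolment stopped at month 5 and a 3-month median, have little of either.

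**What the dilution costs.** If the effect is spread evenly over days after assignment, the detectable difference shrinks by the second figure in each cell. In the plan's formula for two means, *n* varies as 1/d². A 2% share raises the required number by 1/0.98² = 1.04, and a 31% share by 1/0.69² = 2.1, with the variance unchanged.

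**The case against.** The strongest reply is that use in the last 30 days of life is a deliberate question. It is the stated hypothesis, it matches the first specific objective and Phase 1, and Population for Study presents the 150 as a share of deaths, so the design may intend to analyse only decedents. That stands as a reason to keep the measure. It does not make it a sound main outcome after randomisation, because the analysed set is then still chosen by an event after assignment. It does mean that one should not simply subtract survivors from 150, a figure that is provisional in any case.

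A reader might infer that the comparison is biased between the cohorts. The document does not support that in general. If SAIATU does not change survival, both cohorts are followed alike and deaths are ascertained equally, the comparison among the deceased is not biased between arms for use in that window; it is narrower. Days before assignment pull toward zero and do not create a false effect.

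A reader might also infer that all use before the last 30 days is discarded. That is too strong. In Analysis of variables the window is attached to the descriptive study; the paragraphs on tests and costs name none, nor does the cost objective. Home Hospitalisation and SAIATU activity are to be recorded throughout care. What can be said is that the hypothesis, as worded, is confined to the last 30 days.

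Finally, a reader might infer that survivors and early deaths will certainly be numerous. That depends on the assumed survival shape and enrolment. With a rising hazard, a 2-month median and enrolment to month 8, both shares are only about 6%.

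Could the handling of these patients be left to a fuller document? Such detail could be. But the window itself is stated three times, and followed as written it has these consequences.

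**Conclusion.** The point holds as a fault in the stated outcome window. A measure suited to a decedent cohort has been carried into a prospective randomised comparison, where it leaves survivors without an outcome, dilutes the effect in those who die early and leaves earlier use out of the test of the hypothesis. These consequences need no assumption.

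Their size does. Over the assumed range, roughly 0% to 47% of randomised patients are alive at close and 2% to 31% of counted days precede assignment. Nothing in the article narrows this. Bias between the cohorts is conditional on SAIATU changing survival, the timing of use or the ascertainment of death.

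**What to change.** For the randomised comparison, define resource use and cost forward from the date of assignment to death or a common cap, in all randomised patients. The cap must be set before enrolment; the article offers no basis for a particular value, so the sponsor should choose and justify one. A total to death or cap mixes length of survival with intensity of use, so report it with survival time accounted for, for example per day alive alongside the total.

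Take the variance for the sample size formula from a matching window, since the Phase 1 variance describes a different quantity.

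Keep the last-30-days-of-life comparison as a secondary analysis, limited to days after assignment, for comparison with Phase 1.

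Primary and specialised care activity comes from routine Osakidetza records, which can be cut at the assignment date. The cost is some rewording of the hypothesis, some extra analysis, a fresh variance estimate, and a main figure less directly comparable with Phase 1 and the pilot.

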**Discussion:**

The results of this prospective study will assist in verifying or disproving the hypothesis that the in-home social care offered by SAIATU improves the efficiency of healthcare resource usage by these patients (quality of life, symptom control).

This project represents a dramatic advance with respect to other studies conducted to date, and demonstrates how, through the provision of personnel trained to provide social care for patients in the advanced stages of illness, and through strengthening the co-ordination of such social services with existing healthcare system resources, the resulting holistic structure obtains cost savings within the health system and improves the efficiency of the system as a whole.

## Background

In the developed world, some 10,000 people per million population die every year. Some 70% of the total population lives through a period of terminal illness lasting several months before their eventual death, whether it be a type of cancer (2,500 cases per million population) or the final stage of deterioration of non-oncological illnesses (approximately 4,500 cases per million population) [1]. It has been accepted internationally that the largest proportion of healthcare costs incurred by a citizen are generated in the final months of life. We are therefore discussing the largest source of costs to the healthcare system, an issue to which insufficient attention has been paid. In these cases, both the symptoms themselves and the complexity of accompanying circumstances cause a high degree of suffering in the patient and a social and family crisis in his immediate environment, as well as incurring the largest share of healthcare expenditure in the life of each respective patient.

Palliative Care (PC) [2] has been scientifically demonstrated as a truly effective tool in both welfare and organisational terms, complementing appropriate medication and medical care with psychological, social and spiritual support for patients and their careers.

In addition, the final period of illness is accompanied in nearly all cases by a more or less prolonged period of functional deterioration, leading inexorably to the development of a state of dependence on the part of the terminally ill patient, often accompanied by tremendous socio-familial complexity. Thus, the enormous diversity of psycho-social factors that surround every case can generate a wide range of needs, of greater or lesser severity, which need to be attended to routinely, and which, conversely, do not fall within the competencies provided by the health system itself. In fact, such needs are better understood within the social sphere and often include, among others:

- *Need for attention to patient dependency*: assistance with performing the basic and instrumental activities of daily living; reducing as far as possible the loss of sensory capabilities, and facilitating measures which can compensate for such deterioration; training in habits that improve personal autonomy; early warning of loss of autonomy; measures for the safety and protection of the patient; and adaptation of the environment.

- *Needs of carers and the patient’s social support network*: information about available support services; training and capacity-building for professional and/or family carers; development of communication skills to facilitate dialogue with the patient; family rest and respite; reconciliation of care with the professional life of the carer; psychosocial support to prevent burnout; and the exchange of experiences with other carers.

- *Protection of the patient’s social role:* decision-making autonomy and the communication of the final will; companionship; spiritual expression; leisure and entertainment; privacy or intimacy; interpersonal and social relationships.

While the health system is aimed at ensuring comprehensive care for patients and families, addressing those aspects related to healthcare, and encouraging valid solutions to social problems, reality demonstrates that this is often insufficient. When healthcare teams conduct in-home visits, a solid care structure is required, capable of performing all necessary tasks. Indeed, the problem is two-fold: increasingly, such structures are dwindling as a result of the crisis in informal caregivers, while the assistance required, due to patient complexity, calls for an increasing degree of skill.

In effect, changes to the socio-demographic structure, the ageing population, and the increasing incidence of chronic illness, have been accompanied by the weakening of traditional social support networks, diminishing the available number of informal caregivers who, historically, would have offered in-home care as a matter of course [3].

The development of in-home care from the social sector and its expected growth since the entry into force of the Law for the Promotion of Autonomy and Care for People in a Dependent Situation [4] are not yet sufficient to meet current assistance needs. Furthermore, in the absence of clearly defined alternatives, they will evidently be inadequate to provide family support and patient care for increasingly complex cases in the future, especially if improvements to training procedures are not implemented.

### Effectiveness and efficiency of palliative care at a global level

The incorporation of Support Teams for palliative patients into traditional models of patient care (primary attention, specialist care, emergency, residential centres) offers effectiveness in outcomes such as improving control of symptoms [5], reduction of health-care costs [6], appropriate process management, improvements in quality of life outcomes, and patient and family satisfaction [7,8].

At the hospital level, Palliative Care (PC) support teams act with the advice and support of clinical professionals to resolve the specific and complex problems of terminal patients and ensure co-ordination between levels of care. The incorporation of these specialised teams has been demonstrated to effectively reduce the length of hospital stays [9].

This is one of the most commonly used indicators to measure the cost effectiveness of Palliative Care teams. The reduction of average stay length in a hospital patient is directly correlated with a decrease in both the total and indirect costs of hospital care, which is often unnecessarily prolonged [10]. One study conducted in the United States demonstrated a reduction in costs of US$1.8 million per year after the introduction of PC teams in the hospital [9]. Another study, carried out in Spain, found a reduction in the average length of hospital stay, from 25.5 days to 19.9 days, which coincides with the averages of other studies [11]. This study was conducted over two different time periods, one in 1992 under a traditional care regime and one in 2001 with the presence of functional PC teams. Costs were reduced from 5,068 € per patient per year in 1992 under the traditional hospital model to 1,963 € per patient per year in 2001 [12].

The results of other studies conclude that a reduction of 40-70% in hospital costs could be achieved through the provision of specialised Palliative Care support teams [13]. In addition to providing adequate symptom control, the interventions of PC support teams reduced the number of medical tests and interventions, as well as offering support to families, occasionally allowing them to leave the hospital with the security of relying on an onsite support team [14].

Similar results have been encountered in hospital Palliative Care Units (PCUs), where the costs associated with patient care are lower than those in acute care hospitals. In Smith’s 2006 study [15], a cost reduction of 57% was achieved under the Palliative Care mode. Similarly, in a comparative study between PCUs and hospital units, the average cost per patient in the PCU was calculated at US$700 per day, compared with a cost of US $2,500 per day in Intensive Care units [16]. Significant reductions in hospital admissions have also been found in comparative studies in other countries [17]. In addition, as the PCUs are used in the most complex cases, the consistency and effectiveness demonstrated in the follow-up of patients in acute crisis has facilitated a reduction in hospital admissions, visits to emergency departments and intensive care units [17]. Early identification of patients in terminal stages and their transfer to specialised units allows for the appropriate planning of care and ensures its continuity, leading to effective control of symptoms, reduction of nonspecific treatments, and improvements in quality of life for both patients and their families

In the home environment, the teams offer support and advice to primary care professionals through consultation, direct assistance with the evaluation of patients and families, and the design of appropriate therapeutic intervention strategies.

This support ensures co-ordination between levels of care and improves the portfolio of primary care services [18] with regard to their responsiveness to the complexities of terminal patients. For its part, home-based palliative care has demonstrated effectiveness in:

- Reducing the number of hospital admissions, visits to emergency departments and other specialties, and hospital stays (reduction of 8 days on average) [19], which translates to a decrease in healthcare costs [20,21]. In addition, this type of care allows for a reduction in unnecessary visits to primary care providers and in the length of stays in residential centres.

- The highest rate of deaths at home, which translates to an improvement in the satisfaction and quality of life of both patient and family. In addition to generating emotional and psychological advantages and permitting better control of symptoms, death at home translates to a reduction in hospital costs, which can result in a saving of some 4,000 € for hospital stays per patient [22]. Today, the majority of deaths occur in hospital, which could entail greater economic costs (around 58% currently, and rising to 65% by the year 2030). This is despite evidence showing that between 56% and 65% of patients prefer to die at home [23].

Thus, it is evident that Palliative Care experiences are proving successful in terms of quality, effectiveness, efficiency and cost savings. Indeed, it would be reasonable to anticipate that, based on current socio-demographic trends regarding the prevalence of chronic illnesses and the lack of family caregivers at home, social healthcare development models should begin to promote appropriate social welfare support of community networks in order to make them genuinely useful to healthcare.

At first glance, this solution may appear unfeasible, given that the increased cost of providing special training for home-based assistants would be nearly impossible to contend with in the current environment of socio-economic crisis and budgetary cuts. Nevertheless, hypotheses that defend the efficiency of social healthcare could make it clear that, through investment in better social care, the health system could encounter part of the solution for better healthcare, and, through improved efficiency, reduce overall healthcare costs over time.

Despite the fact that the majority of patients within the Basque Country (60%) die in hospitals, hospitalisation does not always offer better quality of life. Furthermore, the practice of hospitalisation leads to the saturation of emergency services and intensive care units [19,24]. As has been demonstrated in other studies consulted in the literature, the majority of people prefer not to have to die in a hospital, which is cold, routine, impersonal, and high-cost. Rather, people have a strong preference for dying at home, which suggests that patient care should be focused there. This, in turn, would generate a societal demand for staff to support terminal stage patients at home.

